### Outcomes

The self-care components including self-care maintenance, self-care management and self-care confidence would be the main outcome variables of the study. These outcomes will be assessed before intervention and two months after intervention. The Persian version of the self-care chronic heart failure index V 6.2 (pSCHFI) scales is used to evaluate self-care components in three groups of study. The SCHFI uses a quantitative, ordinal, self-report and performance-rating scale (Riegel et al.
2009). Both SCHFI and pSCHFI include three scales with 22 questions–10 questions for self-maintenance, six for self-management and six for self-confidence. Each sub-scale is standardized to a possible score of zero to 100. In Persian version of SCHFI, in comparison with the original SCHFI, some grammatical changes had been made and a few words had been deleted or added, however none of those modifications did not change the meaning of the questions. For example, we inserted the phrase "How routinely do you…" at the beginning of many questions of the Self-maintenance sub-scale, instead of using only one sentence at the beginning of subscale, as used in the original SCHFI. In addition, item 4, "Do some physical activity?" was changed to "Do you routinely do your normal life activities such shopping and cleaning?" (Riegel et al.
2009; Siabani et al.
2014).

In order to obtain demographic data and personal health information- as the secondary outcomes-, an investigator-constructed questionnaire has been also administered that included 13 questions about age, sex, living status (with whom they live), smoking, co-morbidities (e.g. hypertension), duration of heart failure, and the number of times a patient had been admitted to hospital due to CHF symptoms from diagnosis CHF. This information will be used to evaluate the likely association between self-care scales and personal characteristics. Data collected by three experienced trained nurses and through interviewing have been conducted at the patient’s home or hospital, according to participant preference, before intervention and two months after intervention.

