### Sample size

According to the following formula and information received from another study of a similar design (Riegel et al.
2009), it was expected the mean increase in self-care would be about 22 units (d = 22).

Hence to have a power of 90% (σ =40, d = 22, Z α/2 = 1.96, Z β =0.1) minimum 60 participants were needed for each group.

Considering a non-response rate of 15%, the sample size for each group would be 60, and total of 180 participants. However, according expert opinions, all 231 patients who had completed the primary interviews conducted to obtain the baseline data, and agreed with remaining in the study were considered to participate in the RCT, therefore, each group would be included 77 patients (Figure 
1).

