### Statistical methods

SPSS version 21 and SAS will be used to analyse data. Using descriptive analysis for descriptive data, analytic biostatistics analysis (e.g. ANOVA, independent t-test and paired t-test) for assessing differences (between two groups, among three groups and before and after for each group) will be applied. Regression models will be used to explore associations between predicting factors (e.g. age, gender and education) and self-care scales, and also association between the effectiveness of each strategy and personal characteristics will be used. We will present frequencies and examine the expected associations between different variables to obtain answers for our research questions and hypothesis. T-tests will be used for continuous and normally distributed variables (e.g. self-care maintenance in terms of gender), chi-squared for nominal variables and other proportions (e.g. age group, sex), and multivariate generalized linear regression will be used for detecting associations between outcomes (e.g. self-care management) and explanatory variables (e.g. gender, education and disease duration). Non-parametric tests (e.g., Wilcoxon rank test and Median test) will be used when variables are found not to be normally distributed.

A summary of the interventional strategies is presented in the Table 
1.

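### The test for each main sub-scale is chosen from its observed distribution, so the quantity compared is not fixed in advance, and one permitted fallback, the Median test, can cost over a third of the efficiency

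*Protocol article*

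**What the plan says.** All references are to the Protocol article.

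- **Outcomes.** Self-care maintenance, management and confidence are the main outcome variables. "Each sub-scale is standardized to a possible score of zero to 100". On timing: "These outcomes will be assessed before intervention and two months after intervention".
- **Primary objectives.** All three sub-scales are compared between each pair of the three groups.
- **Statistical methods, default tests.** Differences are assessed with standard parametric tests: "e.g. ANOVA, independent t-test and paired t-test) for assessing differences (between two groups, among three groups and before and after for each group". The condition is given later: "T-tests will be used for continuous and normally distributed variables".
- **Statistical methods, fallback.** "Non-parametric tests (e.g., Wilcoxon rank test and Median test) will be used when variables are found not to be normally distributed". The section gives no criterion for non-normality and does not choose between the two tests that it names.
- **Statistical methods, regression.** "Regression models will be used to explore associations between predicting factors (e.g. age, gender and education) and self-care scales". Disease duration is also named as an explanatory variable; the baseline self-care score is not. Nothing says that the non-parametric tests replace these models.
- **Sample size.** The target is a mean: "it was expected the mean increase in self-care would be about 22 units (d = 22", with SD 40, a two-sided 5% level and 90% power. The trial enrolled 77 per group.

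**The concern.** A t-test compares means, a Wilcoxon rank-sum test compares rank ordering, and a Median test compares the proportions above the pooled median. Under the stated rule the observed distribution picks among these, sub-scale by sub-scale. The three main outcomes could then be reported on three different quantities, and only one of them matches the mean difference that the trial was sized for.

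The rule also looks at the variable itself, while the assumption behind a t-test or ANOVA concerns its distribution within groups. A score bounded at 0 and 100 and built from six or ten ordinal items can plausibly depart from normality, so the fallback is a realistic prospect, though nothing in the article shows how likely it is.

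The second issue is power. The Median test uses only whether each score lies above or below the pooled median. If it becomes the main comparison, the power calculated for a mean difference no longer applies.

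**Working it through.** **Inputs.** From Sample size: d = 22, σ = 40, z for two-sided 5% = 1.96, 15% non-response, 77 enrolled per group. The article gives no distribution for the scores, so every shape below is an assumption.

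**The plan's own figure.** The usual two-sample formula is n = 2σ²(1.96 + 1.2816)²/d² = 2 × 1600 × 10.507/484 = 69.5, so 70 per group for 90% power before dropout. The stated 60 is not reproduced; 60 gives 85.4% power. That is a separate matter. The check below starts from the 77 actually enrolled.

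**Power of the t-test.** Power = Φ(d/(σ√(2/n)) − 1.96).
- n = 77: Φ(0.55 × √38.5 − 1.96) = Φ(1.453) = 92.7%.
- After 15% loss, 77 × 0.85 = 65.45, taken as 65: Φ(0.55 × √32.5 − 1.96) = Φ(1.176) = 88.0%.

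**Normal data.** Asymptotic relative efficiency (ARE) against the t-test is 4σ²f(median)² for the Median test and 12σ²(∫f²)² for Wilcoxon.
- Median test: 2/π = 0.637, a 36.3% loss. 77 acts like 77 × 0.637 = 49.0, giving Φ(0.55 × √24.5 − 1.96) = 77.7%. 65 acts like 41.4, giving 70.6%.
- Wilcoxon: 3/π = 0.955, a 4.5% loss. Power at 77 per group is 91.5%.

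**Other shapes.** The fallback is meant for non-normal data, so the normal figure is only a benchmark.

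| Assumed shape | Median/t | Wilcoxon/t |
|---|---|---|
| Uniform | 0.33 | 1.00 |
| Beta(2,2) | 0.45 | 0.86 |
| Beta(2,4) | 0.52 | 0.96 |
| Beta(5,2) | 0.55 | 1.01 |
| Gamma(2) | 0.79 | 1.50 |
| Logistic | 0.82 | 1.10 |
| Lognormal(0.5) | 0.93 | 1.58 |
| t, 5 df | 0.96 | 1.24 |
| Exponential | 1.00 | 3.00 |
| Laplace | 2.00 | 1.50 |

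The four bounded shapes lose 45% to 67% with the Median test. Wilcoxon is never below 0.86.

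**Simulation of the switch.** 77 per group, SD 40, shift 22, 3000 runs. Assumed rule: use the Median test if Shapiro-Wilk gives p < 0.05 in either group, otherwise the t-test.

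| Shape | Switch rate | Power: t | Power: Median | Power: rule | Type I: Median | Type I: rule |
|---|---|---|---|---|---|---|
| Normal | 9–10% | 0.937 | 0.791 | 0.922 | 0.056 | 0.058 |
| Uniform | >99% | 0.921 | 0.523 | 0.523 | 0.052 | 0.053 |
| Beta(5,2) | 94% | 0.928 | 0.729 | 0.738 | 0.067 | 0.067 |
| Laplace | 90–91% | 0.923 | 0.983 | 0.979 | 0.048 | 0.048 |

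The shapes were scaled to the plan's SD of 40, so they illustrate shape and not the literal 0–100 range: a uniform with SD 40 has width 40 × √12 = 139. The efficiencies do not depend on scale. The t-test's power stays near 92% in every shape, which supports keeping a mean-based comparison at this sample size.

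**The case against.** **The article is condensed.** A normality criterion and the choice between rank tests could sit in a fuller plan. That is fair, and their absence is not the point. The published rule itself selects the test from the observed outcome, and added detail would refine that rule without removing it.

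**The rule may not govern the main comparison.** It speaks of variables in general, and the t-test example concerns a sub-scale by gender. This stands as a caution. However, the same section assigns t-tests and ANOVA to the group comparisons and carves out no exception for the main outcomes, so the natural reading includes them.

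**The loss belongs to one of two examples.** This stands. Wilcoxon is named first and costs little. Nothing says the Median test would be chosen, and for heavy-tailed data it can gain power.

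**Stronger readings that a reader might infer, and that the document does not support:**
- *The switch drops baseline adjustment.* The planned ANOVA and t-tests name no baseline covariate, so there is none to lose. A Wilcoxon test on change scores would still use the baseline. The lack of adjustment is a separate weakness of the default analysis.
- *The pretest inflates type I error.* The rule gave 0.048 to 0.067, practically the same as the Median test alone.
- *The fallback is what prevents a claim that volunteers do at least as well as professionals.* The default tests do not support that claim either, since no margin is stated.
- *The trial's power is 78%.* That figure is for normal data analysed by the Median test throughout, not the expected power under the plan.

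**Conclusion.** The point holds as a correctable weakness in the analysis rule. The quantity compared on each main sub-scale can depend on the observed data and can differ between sub-scales, while the design rests on a mean difference of 22 with SD 40. This follows from the text and needs no distributional assumption.

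The power cost is conditional on the Median test being used. It is 36% of the efficiency under normality (77.7% against 92.7% power at 77 per arm; 70.6% against 88.0% at 65), and 45% to 67% for the bounded shapes tried. It is smaller or absent for several skewed or heavy-tailed shapes, and Laplace data show a gain. Which of these applies cannot be settled from the article. With Wilcoxon the cost is minor, and the problem is then mainly the shifting quantity. The change should be made; the weakness does not invalidate the design.

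**What to change.** In Statistical methods, state one main analysis for all three sub-scales whatever the normality finding: a linear model of the two-month score on group, adjusted for the baseline score, reporting each pairwise mean difference with its confidence interval. Use robust or bootstrap standard errors if residual variances are unequal or the residuals are clearly non-normal. Delete the switching rule and the Median test. Report a rank-based analysis of all three sub-scales, not only those that look non-normal, as a sensitivity check.

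The baseline adjustment improves the default analysis in the same edit; it does not repair something the switch removed. The baseline score is already collected, so no new data or patients are needed. The cost is analysis wording only. The Results section says that the analysis is not complete, so the change can still be recorded, dated, before the groups are compared.

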**Table 1 Tab1:** **The characteristics of randomized control trial**

Group	GROUP I	GROUP II	Group III
**Intervention (education)**	Strategy I	Strategy II	Control group (Standard care)
**Educators**	CHVs	Formal health educators	-
**Strategy**	Face-to-face	Small group	-
**Duration**	2 hours	4 hours	-
**Participants**	77	77	77
**Setting**	Patients’ homes	Hospital	-
**Materials**	Simplified instruction for self-care provided by a GP and under supervision a cardiovascular specialist	Simplified instruction for self-care provided by a GP and under supervision of a cardiovascular specialist	-
**Monitoring**	Checking 25% of cases by one of investigators for intervention fidelity	An investigator attending in class without announcing	-

## Results

The results of this study will be reported once data analysis is completed.

## Conclusion

This study was designed to examine the hypothesis that CHVs through a face-to-face education program offered at patients’ homes are able to train patients with CHF to care for themselves. If true, this would be a low-cost, simple and possibly more effective educational approach in order to improve self-care in patients with CHF. This strategy, especially in countries with limited resources, can minimize inequity in health services.
